## Hypothesis and objectives

The overall goal of this study is to define a minimum quantitative threshold of T cells induced by vaccination needed to control subsequent infection, independent of antibodies. We will conduct an experimental study in healthy adult volunteers, leveraging on the immunogenic properties of the licensed live-attenuated yellow fever (YF17D; STAMARIL^®^, Sanofi Pasteur) and chimeric Japanese encephalitis-YF17D (JE-YF17D; IMOJEV^®^, Sanofi Pasteur) vaccines. These vaccines contain the same genomic YF17D backbone (13, 14): vaccination with either vaccine would likely produce T cell responses that, like other flaviviruses, are preferentially directed against the non-structural proteins encoded in their shared genomic backbone, and hence would cross-protect against each other (**Figure 1**). YF17D and JE-YF17D, however, encode different structural pre-membrane (prM) and envelope (E) proteins: vaccination with either would produce neutralizing antibodies protective only against that virus (15). Moreover, YF17D and JE-YF17D vaccination induce different levels of infection as determined by vaccine RNAemia (16, 17), and expectedly differing levels of innate immune responses, allowing us to evaluate how RNAemia and innate immune profile shapes T cell response. The properties of these two live-attenuated vaccines thus provide a unique opportunity to differentiate the role of T cell immunity from humoral immunity in controlling viral infection. In addition, we will also use the licensed inactivated Japanese Encephalitis virus (JEV; IXIARO^®^, Valneva) vaccine to control for the effects of cross-reactive anti-flaviviral antibodies, although we have not observed suppression of YF17D RNAemia from inactivated JEV vaccination (16). Overall, we hypothesize that a high CD4+ and CD8+ T cell response will reduce RNAemia upon challenge with a structurally heterologous virus, and correspondingly result in reduced magnitude of host response to challenge infection. The specific objectives of the study are as follows:

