### Study design

56 subjects will be randomized into 1 of 2 arms (Arm 1 and Arm 2) in a 1:1 ratio. These two arms will be double-blinded. Subjects in Arm 1 will receive JE-YF17D vaccine (IMOJEV^®^, Sanofi Pasteur) on Day 0, followed by YF17D vaccine (STAMARIL^®^, Sanofi Pasteur) on Day 28. Subjects in Arm 2 will receive YF17D vaccine on Day 0 followed by JE-YF17D vaccine on Day 28. A separate non-randomized non-blinded cohort of 14 subjects will be recruited into Arm 3. Subjects in Arm 3 will receive inactivated JEV vaccine (IXIARO^®^, Valneva) on Day 0 followed by YF17D vaccine on Day 28. **Table 1** summarizes the study design.

**Table 1 T1:** Study design.

Arms	Vaccination schedule	
	1^st^ vaccination (Day 0)	2^nd^ vaccination (Day 28)
Arm 1* (n=28)	JE-YF17D vaccine (IMOJEV^®^, Sanofi Pasteur)	YF17D vaccine (STAMARIL^®^, Sanofi Pasteur)
Arm 2* (n=28)	YF17D vaccine (STAMARIL^®^, Sanofi Pasteur)	JE-YF17D vaccine (IMOJEV^®^, Sanofi Pasteur)
Arm 3** (n=14)	Inactivated JEV vaccine (IXIARO^®^, Valneva)	YF17D vaccine (STAMARIL^®^, Sanofi Pasteur)

*Subjects (n=56) will be randomized in a double-blind manner to either Arms 1 or 2. **A separate cohort (n=14) will be recruited into Arm 3 in a non-randomized, single arm, open label design.

The rationale for these three study arms is as follows: Arm 1 will show the impact of a lower level of RNAemia induced by JE-YF17D vaccination (as compared to YF17D vaccination), and the resultant lower levels of virus-specific CD4+ and CD8+ T cells, would have on YF17D infection. In contrast, YF17D vaccination in Arm 2 would produce higher levels of RNAemia (as compared to JE-YF17D vaccination), and in turn higher levels of virus-specific T cells, thus likely resulting in greater suppression of JE-YF17D infection. The first vaccination in Arms 1 and 2 would provide the RNAemia response in the absence of virus-specific T cells, which would serve as a reference point to interpret the outcome of the second vaccination. For example, the level of suppression of JE-YF17D RNAemia will be the difference in RNAemia levels between subjects who received JE-YF17D as a second vaccination (Arm 2) compared to those who received it as a first vaccination (Arm 1), and similarly for YF17D vaccine. Arm 3 will serve as the control arm, as vaccination with inactivated JE vaccine should not produce any YF17D-specific T cell response.

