### Sample size calculation

To detect an effect size of 0.8 SD in mean RNAemia level on log (10) scale between the first and second dose with the same vaccine – first dose of YF17D will be analysed against those who received YF17D after JE-YF17D and vice versa – a sample size of 25 per group will provide 80% power at a 5% two-sided type 1 error rate. To allow for a drop-out rate of 10%, a total sample size of 28 per group for Arms 1 and 2 is targeted. For Arm 3, which is the control group, a sample size of 14 will be used.

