Linear regression analysis between peak RNAemia and T cell responses will performed to determine the minimal level of T-cell responses needed to reduce peak RNAemia by 1 log genome copies/ml. If, however, the correlation is non-linear (p > 0.05) a polynomial fit will be used to evaluate if a good model fit can be attained. Finally, in the unlikely event that none of these models fit the data points, the T-cell response for all subjects will be consolidated, and the T-cell responses that are at least 3 standard deviations away from the mean T-cell responses will be determined. These data points will be labelled as outlier responses, and the corresponding level of fold-change reduction in RNAemia will be determined. For all statistical comparisons, a p-value of <0.05 will be considered significant.

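### The T-cell threshold rule reads p > 0.05 as non-linearity, and its 3-SD fallback does not estimate the T-cell level for a 1 log reduction

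*Protocol article*

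**What the plan says.** Under Hypothesis and objectives, the protocol article gives the overall goal of the study: to "define a minimum quantitative threshold of T cells induced by vaccination needed to control subsequent infection, independent of antibodies". The last paragraph of Data and statistical analysis is the only place that says how this threshold is obtained. It sets three steps.

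1. Peak RNAemia is regressed linearly on T-cell response, to find the smallest response that lowers peak RNAemia by 1 log genome copies/ml.
2. "If, however, the correlation is non-linear (p > 0.05) a polynomial fit will be used", to see whether a good fit can be reached.
3. If neither model fits, which the article considers unlikely, all subjects are pooled and the "T-cell responses that are at least 3 standard deviations away from the mean T-cell responses will be determined". These are labelled outliers, and the matching fold-change reduction in RNAemia is reported.

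The article gives no other test of linearity or lack of fit.

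**The concern.** Steps 2 and 3 are stated rules, not detail left for later, and neither does what it is meant to do.

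Step 2 uses a p-value to decide between a straight line and a curve. The usual p-value beside a linear regression or correlation tests whether the slope is zero. A large value is what a weak relation, or none, produces. A small value is what many curved relations produce as well. The rule therefore cannot separate linear from non-linear. If the p-value were meant as a lack-of-fit test, the direction would be reversed, because p > 0.05 would then be the result that does not reject linearity.

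Step 3 selects subjects on T-cell response alone, counts unusually low as well as unusually high responses, and ends in a fold-change in RNAemia. The goal asks for the inverse quantity: the T-cell level that goes with a given reduction.

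At stake is the study's main interpretive output. The Discussion says that the minimum threshold would be foundational for choosing vaccine candidates.

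**Working it through.** **The plan's own figure.** The only computed figure in the article is the sample size: "To detect an effect size of 0.8 SD in mean RNAemia level on log (10) scale", "a sample size of 25 per group will provide 80% power at a 5% two-sided type 1 error rate". Normal approximation: n = 2 × (1.960 + 0.842)² / 0.8² = 2 × 7.849 / 0.64 = 24.5, so 25 per group. Drop-out: 25 / 0.9 = 27.8, so 28. Noncentral-t power at 25 per group is 79.2%, close to the stated 80%. With 56 in Arms 1 and 2 and 14 in Arm 3, the total is 70. These figures reproduce. They concern a comparison of two means; the threshold rule has no operating characteristics of its own.

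**Check 1: a linear truth sent to the polynomial.** The inputs are the 0.05 level (stated) and the correlation r between T-cell response and peak RNAemia (assumed, as the article gives none). The article does not say whether the regression is run per arm or pooled, so n is taken as 25 (one arm after drop-out), 56 (Arms 1 and 2) and 70 (everyone).

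Approximation: P(p > 0.05) ≈ Φ(1.96 − atanh(r) × √(n − 3)).

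Example, n=25 and r=0.3: atanh(0.3) = 0.3095 and √22 = 4.690, with product 1.452. Then 1.96 − 1.452 = 0.508 and Φ(0.508) = 0.69. Simulation of the t-test on the slope gives about the same:

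| n | r = 0 | r = 0.3 | r = 0.4 |
|---|---|---|---|
| 25 | about 95% | about 68% | about 48% |
| 56 | about 95% | about 38% | about 13% |
| 70 | about 95% | about 28% | about 6% |

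The r = 0 column is 1 − 0.05 by construction, whatever the n.

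**Check 2: a non-linear truth kept as a line.** The assumed truth is a 1 log step at the mean T-cell response. With residual SD 0.5 log, the linear p-value is at or below 0.05 in 95% of trials at n=28 and in essentially all trials at n=56 and n=70. With residual SD 1.0 log, the figures are 49%, 80% and 89%. So the rule often keeps a straight line when the truth is a step.

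**Check 3: what happens after p > 0.05.** Suppose that a good polynomial fit means an overall p < 0.05 (an assumption, as the article gives no criterion). Among linear or null truths with linear p > 0.05, at n = 25 to 70, a quadratic then passes in only about 0 to 7% of cases. Most such cases would go on to step 3.

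**Check 4: the 3-SD step.** For normal responses with known mean and SD, P(|z| ≥ 3) = 0.0027. The expected number of subjects at N=70 is 70 × 0.0027 = 0.19, and P(none) = (1 − 0.0027)^70 = 83%. Simulation with the sample mean and SD, as the rule would be applied:

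| T-cell distribution (assumed), N=70 | Nobody flagged | Mean number flagged |
|---|---|---|
| Normal | 87% | 0.14 |
| Log-normal, ln-SD 0.25 | 55% | 0.5 |
| Log-normal, ln-SD 0.5 | 21% | 1.0 |
| Log-normal, ln-SD 0.8 | 5% | 1.5 |

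Whichever row applies, the output is the RNAemia change of those subjects, not a T-cell level.

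**The case against.** Several points on the other side have weight.

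- A reader might infer that the rule picks the wrong model as a matter of course. The documents do not support that. If all 70 subjects are pooled and r is 0.4 or more, the straight line is kept in about 94% of trials or more. The high misrouting rates belong to small n or weak correlation, and the article fixes neither.
- A reader might infer that the fallback usually comes back empty. That needs near-normal T-cell responses. The article states no distribution and allows for non-normal data elsewhere in the same section. With moderate right skew, one or two subjects are usually flagged. The sound criticism is that the step does not estimate the threshold at all.
- A reader might infer that a threshold must be a hinge or plateau, so that a straight line is wrong in itself. The article defines its target as the level giving a 1 log reduction, which is a point on a curve and can be read from a line. Nor can a bias in the threshold be given from the documents, because it depends on an assumed curve, spread and residual SD.
- The polynomial is only to be evaluated, not adopted automatically, so over-fitting is not the main consequence. But Check 3 then makes the fallback less unlikely than the article says.
- The threshold is the overall goal but is not among the listed primary or secondary objectives, and an SAP may add detail. This bears on weight. It does not repair a rule that the article states and that is wrong on either reading of the p-value.

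**Conclusion.** The concern holds in this form. The p > 0.05 rule is not evidence of non-linearity, and the model choice built on it can be wrong in both directions. That conclusion is logical and needs no assumption. Its size does: over r = 0.3 to 0.4 and n = 25 to 70, between about 68% and 6% of truly linear relations would be called non-linear, and about 95% of null relations at any n. The 3-SD fallback does not deliver a T-cell level for a 1 log reduction under any distribution. At N=70 it would rest on nobody in about 87% of trials if responses are near normal, and on about 0.5 to 1.5 subjects on average if they are log-normal with ln-SD 0.25 to 0.8. The correlations, residual SDs and distributions are assumptions. The powered comparison of RNAemia between first and second dose, and its sample size, are not affected.

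**What to change.** Rewrite the threshold paragraph of Data and statistical analysis.

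- Name one monotone alternative to the straight line in advance, on log10 T cells. Choose between the two by a lack-of-fit test or AIC, not by the slope p-value. The form of the alternative (segmented or logistic, for example) is the sponsor's choice.
- Report the T-cell level for a 1 log reduction in peak RNAemia with a 95% CI (Fieller or bootstrap).
- Delete the 3-SD step. If there is no association, or the interval is unbounded, state that no threshold was identified and describe RNAemia reduction by T-cell tertile.

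The cost is one paragraph, with no new data or visits. The downside is that the threshold may come with a wide interval or not be identified. AIC will also not always find the right shape in small samples: with an assumed moderate hinge at n=25 and residual SD 0.7, it chose the hinge in only about 56% of runs. The interval should therefore carry the conclusion, not the selected model.

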## Safety assessment

### Definitions

An adverse event (AE) is any untoward medical occurrence in a patient or clinical investigation subject administered a pharmaceutical product and which does not necessarily have a causal relationship with this treatment. An AE can therefore be any unfavorable and unintended sign (including an abnormal laboratory finding), symptom, or disease temporally associated with the use of a medicinal (investigational) product, whether or not related to the medicinal (investigational) product.

A serious adverse event (SAE) is any untoward medical occurrence that at any dose results in death, is life-threatening, requires inpatient hospitalization or prolongation of existing hospitalization, results in persistent or significant disability/incapacity, or is a congenital anomaly/birth defect.

AEs will be graded according to the Common Terminology Criteria for Adverse Event Monitoring, version 5.0. Event terminology, the date and time of event start and end, severity, relatedness, impact to the continuation of the study, and final outcome of the event will be recorded on the case report form from day 0 to the last study visit until the event has been resolved. For a SAE, in addition to the above, an event summary, the criteria used to categorize the event as an SAE, and a list of all tests and treatments given for the event will be documented.

### Serious adverse event reporting

SAE reporting requirements will be in accordance with the SingHealth CIRB protocols. Only related SAEs (definitely/probably/possibly) will be reported to CIRB. Related means there is a reasonable possibility that the event may have been caused by participation in the clinical trial. The PI will be responsible for informing CIRB after first knowledge that the case qualifies for reporting. Follow-up information will be actively sought and submitted as it becomes available. Related AEs (non-SAE) will not be reported to CIRB. However, the investigator is responsible to keep record of such AEs cases at the Study Site File.

All SAEs that are unexpected and related to the study drug will be reported to Health Sciences Authority (HSA) of Singapore. The PI is responsible for informing HSA no later than 15 calendar days after first knowledge that the case qualifies for expedited reporting. Follow-up information will be actively sought and submitted as it becomes available. For fatal or life-threatening cases, HSA will be notified as soon as possible but no later than 7 calendar days after first knowledge that a case qualifies, followed by a complete report within 8 additional calendar days.

### Study monitoring

The study may be evaluated by government inspectors/regulatory authorities who must be allowed access to electronic case report forms (CRFs), source documents, and other study files. The inspectors will review CRFs and compare them with source documents to verify accurate and complete collection of data and confirm that the study is being conducted according to the protocol, ICH-Good Clinical Practices and all applicable regulations.

## Discussion

Although this study is focused on flaviviral vaccines, T cell immunity also plays a critical role in other viruses and viral vaccines. For example, although current COVID-19 mRNA vaccines are not able to sustainably protect against infection by the Omicron variant due to antibody escape mutations, protection against severe disease is maintained through preserved virus-specific T cell responses (23–28). We have also previously shown that the induction of T cell responses coincide with the onset of COVID-19 vaccine-induced protection, even prior to the appearance of neutralizing antibody responses (29). Thus, the findings from this trial would be applicable to many viral diseases.

The experimental medicine approach will enable the systematic study of the host T cell immune response to both vaccination and acute viral infection in a safe, controlled and ethical manner. In contrast, a “real world” study involving patients naturally infected with wild-type virus would be confounded by multiple factors, including virus strain variations and size of virus inoculum. As the exact timing of infection would be unknown, such studies would also encounter difficulty in obtaining pre- and post-infection samples at fixed time-points, and would require an unfeasibly large sample size in order to successfully test our hypotheses.

It can be argued that this study makes use of attenuated viruses, and thus the magnitude and quality of protective T cell responses measured would underestimate the threshold needed for immunity against wild-type virus as well as non-flaviviruses. Although this argument holds, our goal, however, is not to define a universal T cell correlate of protection. Rather, we submit that the use of attenuated viruses would establish a minimum threshold – the quantity and quality of T cell responses below such a threshold would unlikely be able to control any systemic wild-type viral infection. Such information would be foundational when selecting promising vaccine candidates for further clinical development.

## Ethics statement

The studies involving human participants were reviewed and approved by SingHealth Centralised Institutional Review Board. The patients/participants provided their written informed consent to participate in this study.
